### Informed consent and randomization

Patients are first informed on the study during the preoperative screening program, which consists of consultations with a surgeon, an internist, a dietician, a psychologist, and meetings for patient education. If patients proceed towards surgery, they are screened for inclusion into the study. Patients are asked for written informed consent to participate in the study by the surgeon and also to store study materials in the DIABAR-biobank. After informed consent is obtained by the surgeon at the outpatient clinic, patients will be randomly assigned by the surgeon to undergo a RYGB or OAGB in a 1:1 ratio. Randomization will be performed with the use of electronic block-randomization with the program *Castor Electronic Data Capture* (Ciwit BV, the Netherlands). Block size varies between four and six; there is no stratification. Patients and surgeons are directly informed on the outcome of the randomization.

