### Study design and sites

The DIABAR-trial is a two-armed, multi-center, open randomized controlled clinical trial comparing the effect of the RYGB (control) and the OAGB (intervention) on glycemic control. Participating centers are the Spaarne Gashuis (Hoofddorp, the Netherlands), MC Slotervaart (Amsterdam, the Netherlands), and the Franciscus Gasthuis (Rotterdam, the Netherlands). The DIABAR-trial started in October 2017 at MC Slotervaart (Amsterdam, the Netherlands) and the trial continued in March 2019 at the Spaarne Gasthuis (Hoofddorp, the Netherlands) by the same surgical staff and research team. In August 2020, the Franciscus Gasthuis (Rotterdam, the Netherlands) was added as a participating center. Materials will be stored in the DIABAR-biobank, which is located in the affiliated Amsterdam University Medical Center (AUMC) (Amsterdam, the Netherlands). Study materials will be processed in the laboratory of the AUMC and in the Wallenberg laboratory (University of Gothenburg, Gothenburg, Sweden).

The DIABAR-trial is closely related to the BARIA-study, a longitudinal cohort study in 1500 patients with severe obesity. In the BARIA study, systems biology is used to identify microbial, immunological, and metabolic markers for metabolic response prior to and after bariatric surgery [15]. The BARIA-study is conducted at the Spaarne Gasthuis and the existing infrastructure of the BARIA-study can be used in the DIABAR-trial. This explains why patients participating from the Spaarne Gasthuis will be asked to partake in a more extensive study protocol than patients enrolling from the Franciscus Gasthuis (Table 1). In Fig. 1 an outline of study enrolment, randomization, intervention and follow-up is shown.

**Table 1 Tab1:** Study procedures in the Spaarne Gasthuis and the Franciscus Gasthuis

		Enrolment allocation	Post-allocation								
Timepoint		***t***=-2	***t*** = -1	***t*** = 0	***t*** = 1	***t*** = 2	***t*** = 3	***t*** = 4	***t*** = 5	***t***=6-9	***t***=10
	Medical center	Screening	< 42 days of surgery	Day of surgery	14 D	42 D	6 M	1 Y	2 Y	3,4,5,10 Y	Re-operation^**a**^/endoscopy

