### Exclusion criteria

Patients will be excluded on the following basis:Known genetic basis for insulin resistance or glucose intoleranceType 1 diabetes mellitusPrior bariatric surgeryAuto-immune gastritisGastro-esophageal reflux disease (confirmed by endoscopy or the use of a proton-pump inhibitor indicated by complaints of gastro-esophageal reflux)Known presence of a large hiatal hernia requiring concomitant surgical repairCoagulation disorders or a hemoglobinopathyUncontrolled hypertension (RR > 150/95 mmHg)Renal insufficiency (creatinine > 150 μmol/L)Pregnancy or breastfeedingAlcohol or drug dependencyParticipation in any other therapeutic study that may influence primary or secondary endpointsPatients who are considered incapable to fully understand the study and implications of participation in the study (e.g., as a consequence of a language barrier, psychiatric disease or mental disabilities) as judged by the coordinating researcher or the surgeon

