### Trial status

The first patient was enrolled and randomized on October 23, 2017. The study is ongoing. At the time of writing, 86 patients are enrolled in the Spaarne Gasthuis and 14 in the Franciscus Gasthuis. Recruitment is estimated to be completed in 2024. Current trial protocol is version 8.1, July 2020.

Results of the trial will be presented in a manuscript and offered to a peer-reviewed journal.

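### Small, published block sizes in an open trial where the surgeon consents, randomises and learns each result allow partial prediction of the next arm

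*Protocol article*

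**What the plan says.** All places are in the Protocol article.

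- **Study design and sites:** "The DIABAR-trial is a two-armed, multi-center, open randomized controlled clinical trial". The same surgical staff and research team carried the trial from the first hospital to the second in March 2019. A further centre joined in August 2020.
- **Informed consent and randomization, screening:** "If patients proceed towards surgery, they are screened for inclusion into the study". No actor is named.
- **Same section, sequence of steps:** consent comes first and is taken by the surgeon. The same person then makes the allocation: "patients will be randomly assigned by the surgeon to undergo a RYGB or OAGB in a 1:1 ratio". The tool is electronic (Castor). Patients and surgeons learn the result directly.
- **Same section, blocks:** "Block size varies between four and six; there is no stratification". With no stratification, the natural reading is one list shared by all centres.
- **Exclusion criteria:** inability to understand the study is a judgement criterion, "as judged by the coordinating researcher or the surgeon".
- **Trial status:** "86 patients are enrolled in the Spaarne Gasthuis and 14 in the Franciscus Gasthuis". Recruitment is expected to finish in 2024, so the block sizes were published with roughly 100 of 220 patients enrolled.

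**The concern.** Concealing each assignment is not the same as making it unpredictable. In a blocked 1:1 sequence every block must end balanced, so a recruiter who remembers recent open allocations knows which arm is owed. The shorter the blocks, the sooner that debt must be paid, and knowing the permitted sizes sharpens the guess.

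Here the person who takes consent also triggers randomisation, learns the result and may apply a judgement exclusion. A recruiter who expects a given arm next could delay consent, choose whom to approach, or apply that exclusion differently. Any such selection would act before randomisation, so analysing patients in their allocated arm would not remove it. Insulin use and diabetes duration are known to clinicians at that stage, and the Discussion says that randomisation is not stratified on them.

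**Working it through.** The article gives no predictability figure, so there is none to reproduce. The check asks how well the next arm can be guessed under the stated scheme.

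**Inputs.** From the article: 1:1 ratio, block sizes four to six, no stratification, 220 patients, 86 of 100 reported patients at one centre. A block of five cannot be balanced at 1:1, so the sizes are 4 and 6. Assumption: the two sizes are equally likely.

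**Step 1: block boundaries known (exact).** The best guess at any point is right with probability max(remaining A, remaining B) / total remaining.

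- Block of 4: the expected values over the four positions are 1/2, 2/3, 2/3 and 1. Their sum is 2.833, and 2.833/4 = 70.8% correct. The next arm is certain at position 4 always and at position 3 with probability 1/3, so (1 + 1/3)/4 = 33.3% are certain.
- Block of 6: full enumeration gives 68.3% correct and 25.0% certain.
- Equal mix, weighted by patients: (4 × 70.8 + 6 × 68.3)/10 = 69.3% correct, and (4 × 33.3 + 6 × 25.0)/10 = 28.3% certain.

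**Step 2: sizes known, boundaries not known (simulation of 220 allocations).** The observer updates by Bayes' rule over block size and position and guesses the likelier arm. Visibility is the share of past allocations whose arm the observer learns. An unseen allocation is known to have happened, but not to which arm, which favours the observer.

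| Blocks | Visibility | Best guess right | Probability ≥ 0.75 | Certain |
|---|---|---|---|---|
| 4, 6 | 100% | 69.2% | 49.6% | 5.4% |
| 4, 6 | 86% | 64.9% | 30.5% | 2.4% |
| 4, 6 | 50% | 58.5% | 6.7% | 0.2% |
| 4, 6 | 25% | 55.0% | 1.0% | 0% |
| 8, 10, 12 | 100% | 65.1% | 20.4% | 1.2% |
| 8, 10, 12 | 86% | 60.7% | 7.4% | 0.2% |

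Chance is 50%. Varying the block size already cuts certain calls from 28.3% to 5.4%, but it leaves the correct-guess rate almost unchanged (69.3% against 69.2%).

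**Step 3: what a guess could do (illustration only).** Suppose a recruiter shifted expected HbA1c by +d when guessing one arm and by −d when guessing the other, for every patient. With correct-guess rate p, the between-arm bias is 2d(2p − 1):

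- p = 0.692: 0.77d
- p = 0.649: 0.60d
- p = 0.585: 0.34d

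For an arbitrary d of 0.25 percentage points these are 0.19, 0.15 and 0.09 points. For scale, 100 per group with 80% power and two-sided 5% detects SD × √(2/100) × (1.960 + 0.842). That is 0.55 points at SD 1.4 and 0.59 at SD 1.5, if the pre-operative SDs in the sample-size section also applied at 12 months. The article gives no basis for any value of d.

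**The case against.** The strongest reply is that the full-visibility figures describe an observer whom the article does not show. It does not say how many surgeons randomise, or whether they follow one another's results. On one shared list, a surgeon who sees a quarter to a half of allocations is right only 55 to 59% of the time. The 86:14 split is cumulative, while the smaller centre joined only in August 2020, so its share of current recruitment may exceed 14%. The calculation also assumes perfect tracking over years. All of this stands, and it is why the result is a range.

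The existing safeguards also count. Allocation is electronic and follows consent, so the next arm cannot be looked up, and block size varies. Telling surgeons the arm is unavoidable, since they perform the operation.

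A reader might infer several stronger things that the text does not support:

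- **That the surgeon screens patients.** The screening sentence names nobody.
- **That one person controls eligibility.** The judgement exclusion is shared with the coordinating researcher and concerns only capacity to understand the study.
- **That the next arm is often predictable.** That holds only near full visibility.
- **That imbalance in insulin use or diabetes duration would go uncorrected.** The analysis section plans multivariate analysis without naming covariates, so adjustment is not ruled out.

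What survives is that the block sizes are small, in print during recruitment, and known to people who recruit and learn every result of their own.

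**Conclusion.** The point holds as a moderate weakness in the unpredictability of allocation, worth correcting while about 120 of the 220 patients (220 − 100) remain to be recruited. Over visibility from 50% to 100%, the best guess is right for about 59 to 69% of patients, and about 7 to 50% of allocations can be called with probability 0.75 or more. At 86%, the larger centre's reported share, the figures are about 65% and 31%.

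These rest on sizes 4 and 6 being equally likely, one list across centres, and an observer who tracks optimally. The documents show an opportunity for selection bias. A reader might go on to infer that patients have been steered or that the comparison is already biased; nothing in the article supports that.

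**What to change.** 1. **Main change.** For the remaining patients, switch the randomisation system to larger, randomly varied blocks, for example 8, 10 and 12. Do not disclose the new sizes to recruiting staff, or in any publication before recruitment ends. Even to an observer who knew the new sizes, the share of allocations predictable at 0.75 or more falls from about 50% to 20% at full visibility and from about 31% to 7% at 86%. The correct-guess rate falls less, from about 69% to 65% and from 65% to 61%. Non-disclosure adds protection that these figures do not count.
2. **Secondary change.** Lock the eligibility record electronically before randomisation can be triggered, where possible by existing research staff and not the consenting surgeon. This prevents eligibility being revisited once the arm is known. It does not itself prevent prediction, because operating surgeons still learn the allocations.

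**Cost.** A system setting, a change in delegated tasks and a dated protocol note. Whether research staff are present at each clinic when consent is taken is not stated, hence the wording of the second step. The statistical price is a possible final imbalance: an unfinished block of 12 can leave the arms at most 6 apart, for example 113 against 107, which is negligible at 220. Completing the current block before the switch avoids adding to it.

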**Enrolment/allocation**											
Eligibility screen	SG/FG	x									
Informed consent and allocation	SG/FG	x									

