**Questionnaires**											
Psychological questionnaires	SG/FG		x				x	x	x	x	
GIQLI	SG/FG		x					x	x	x	
Dietary and satiety list	SG		x					x	x		

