### Outcome measures

The primary outcome measure of the DIABAR-trial is glycemic control, as measured by the difference in Hba1c 12 months after RYGB and OAGB. Glycemic control at 6 months, 2–5 and 10 years of follow-up, and the remission of T2DM at 1–5 and 10 years of follow-up are secondary outcome measures. For remission of diabetes, we will use the proposed definition according to ADA consensus report 2021 primarily (Hba1c < 6.5%), and in a secondary analysis, the more strict cut-off < 5.7% will be used [19]. Other secondary outcome measures are related to the interplay of obesity, NAFLD/NASH, and cardio-vascular performance. Table 1 shows the schedule of enrolment and study procedures (SPIRIT-format). All measurements will be performed by the researchers and physicians according to a standard operating procedure.

*Demographics* consist of age, sex, ethnic background, medical history, use of medication, history of weight-change, intoxications, educational level, employment status, and physical activity. Prior to surgery, patients will be asked about their expectations of metabolic surgery in terms of weight loss.

*Biometric data* consist of weight, height, waist to hip ratio, temperature, bioelectrical impedance (BIA), electrocardiogram (ECG), blood pressure, pulse, stroke volume, cardiac output, and systemic vascular resistance (Nexfin).

*Dutch versions of validated questionnaires* are used for evaluation of psychological measures. This includes quality of life, self-efficacy, hunger and craving, social support, depression, and body image, as previously described in the protocol of the BARIA-study [15]. Food intake is registered using food diaries. Gastro-intestinal complaints are assessed with the gastro-intestinal quality of life (GIQLI) questionnaire [20].

*Peripheral blood* will be drawn at various time points as part of the regular follow-up and includes hemoglobin, leukocytes, C-reactive protein, HbA1c, glucose, c-peptide (only baseline), electrolytes, kidney function, hepatic enzymes, lipid profile, iron, vitamins, and thyroid profile.

*Mixed meal test*, a 2-h oral mixed meal test (MMT), will be performed three times in the course of the study [21]. During the MMT, the patient will consume two 125 ml Nutridrink compact drinks (Nutricia®). At set time points during this test, blood will be obtained through an intravenous line and will be used to measure insulin sensitivity, plasma metabolites, and bile acids.

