The underlying physiological and molecular mechanisms responsible for the antidiabetic effects of metabolic surgery have not been fully understood. Proposed theories include acute reduced caloric intake possibly-in part-responsible for the weight-independent antidiabetic effect occurring directly post-surgery, as well as a middle-to long-term antidiabetic effect of surgery-induced weight loss [50]. Rapidly occurring enhanced glycemic control might also be due to altered anatomy and signaling/sensing of the gastro-intestinal tract, formulated in the foregut and hindgut hypothesis [51, 52]. Among other factors that are recognized to be of potential influence are the immune system, the intestinal microbiome, and altered bile acid metabolism [53–56]. Also, there is an association between obesity, non-alcoholic fatty liver disease (NALFD), and insulin resistance/T2DM, with reports of the presence of (some form of) NAFLD in up to 80% of patients undergoing weight loss surgery [57, 58]. It is likely that not one (dominant) factor or one mechanism is responsible for the beneficial glucoregulatory effects of metabolic surgery but that the effects are due to an interplay of various pathways. The DIABAR-trial grants the unique opportunity to assess extensive data of patients with T2DM and obesity after two different metabolic procedures and to explore driving mechanisms in metabolic response.

A few limitations have to be acknowledged. First, for logistic reasons, patients will not be stratified upon the use of insulin or the duration of T2DM. Second, the authors are aware of and responsible for the extent of the study procedures patients are subjected to. Therefore, the study is performed by a research nurse, who stays in close contact with participating patients and monitors how patients perceive their participation in the study. To meet with the patient’s time investment, patients receive a financial reimbursement. Third, patients are required to lose weight prior to surgery. This might influence the metabolic changes induced by surgery; yet patients in both arms of the study are projected to the same pre-surgical weight loss and it lowers the surgical risk.

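### Self-reported baselines (psychological questionnaires, GIQLI, dietary and satiety list) are collected after patients know their operation, so they are not pre-randomisation values

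*Protocol article*

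**What the plan says.** The protocol article (Study design and sites) describes a "two-armed, multi-center, open randomized controlled clinical trial". Under Informed consent and randomization, the surgeon obtains consent at the outpatient clinic and then randomises, and "Patients and surgeons are directly informed on the outcome of the randomization".

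Table 1 gives the same order. The row "Informed consent and allocation" is marked only in the t = -2 (screening) column, for both centres. The heading "Post-allocation" begins with the next column, t = -1, which lies within 42 days of surgery. The row "Psychological questionnaires" and the GIQLI row (both centres), and the dietary and satiety row (Spaarne Gasthuis only), have their first mark at t = -1. Their screening cells are empty.

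Under Analysis of endpoints, continuous data are to be compared by t test or Mann-Whitney U, and multivariate analysis and repeated-measures ANOVA are also named. The article does not say whether the t = -1 score enters those models.

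**The concern.** A baseline is safe to subtract or adjust for when the allocation cannot have influenced it. Measuring it before randomisation guarantees that. Here the patient answers questions on mood, quality of life, gut symptoms and eating after learning which operation will follow.

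The article itself gives a reason why the answers might differ by arm. Its Discussion describes OAGB as controversial because of biliary reflux, and RYGB as carrying a risk of internal herniation. A patient told of either may report differently before surgery.

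At stake is the comparison of patient-reported outcomes, which are among the secondary outcomes. GIQLI also bears on the stated aim of comparing side effects. A pre-allocation value that was never collected cannot be recovered later.

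**Working it through.** **Step 1: order of events.** The article gives no figure to reproduce on this point, so the check is a reading of Table 1 against the text.

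| Item | First scheduled | Pre-allocation value scheduled? |
|---|---|---|
| Consent, allocation, disclosure | t = -2 | not applicable |
| Psychological questionnaires (both centres) | t = -1 | no |
| GIQLI (both centres) | t = -1 | no |
| Dietary and satiety list (Spaarne Gasthuis) | t = -1 | no |

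The text and the table agree: disclosure comes first and the questionnaires follow.

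**Step 2: how a shift would travel.** Scale baseline and follow-up scores to SD 1, with correlation r. Assume no true difference between arms. Let disclosure shift one arm's baseline by s without changing its follow-up score. The absolute bias in the between-arm difference is then:

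- change from baseline: s
- baseline-adjusted (ANCOVA): r × s
- follow-up score only: 0

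A repeated-measures ANOVA that includes the t = -1 score behaves like the first line in its arm-by-time contrast. With two time points, that contrast is the change-score comparison.

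**Step 3: illustration.** The values of s and r are assumptions; the document gives neither. I take s = 0.1 to 0.3 SD and r = 0.3 to 0.7, with n = 100 per arm (the article's required number) and a two-sided 5% level. By the normal approximation:

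- SE of the change-score difference = √(2(1 − r)) × √(2/n)
- SE of the ANCOVA difference = √(1 − r²) × √(2/n), with √(2/100) = 0.1414
- false-positive rate = Φ(bias/SE − 1.96) + Φ(−bias/SE − 1.96)

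| s | r | Change score: bias, SE, false-positive rate | ANCOVA: bias, SE, false-positive rate |
|---|---|---|---|
| 0.1 | 0.3 | 0.10, 0.167, 9.2% | 0.03, 0.135, 5.6% |
| 0.2 | 0.5 | 0.20, 0.141, 29.3% | 0.10, 0.122, 12.9% |
| 0.3 | 0.7 | 0.30, 0.110, 78.2% | 0.21, 0.101, 54.8% |

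With no shift, each rate is 5%. The dietary and satiety list is completed at one centre only, so its n is smaller and the rate for a given s would be lower.

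**Step 4: precision given up by ignoring the baseline.** The SE of a follow-up-only comparison, relative to ANCOVA, is 1/√(1 − r²): 1.05 at r = 0.3, 1.15 at r = 0.5 and 1.40 at r = 0.7.

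**The case against.** The strongest reply is that the bias is doubly conditional. Disclosure must shift answers differently in the two arms, and the baseline must enter the comparison. Both arms receive a gastric bypass, and the document offers no evidence of a shift or of its direction. Nor does the article commit to a change-score or baseline-adjusted analysis of these scales; that detail may sit in an analysis plan that is not shown. All of this stands, and it limits the point to an avoidable risk. It does not alter the order of events.

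A second reply is that follow-up questionnaires are also answered with the arm known, so reordering the baseline does not make the patient-reported outcomes unbiased. That is true of any open trial. It is a separate source of bias and no reason to keep this one. Complications are events after surgery, reviewed by an independent adjudication committee, and are not touched.

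Several stronger readings are tempting, but the document does not support them:

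- **Expected weight loss.** A reader might infer that expectations are recorded with the arm known. The text says only "Prior to surgery, patients will be asked about their expectations of metabolic surgery in terms of weight loss", and Table 1 has no row for it, so its timing relative to randomisation is open.
- **Mixed meal test.** It also first appears at t = -1, but it is an objective blood test done at Spaarne Gasthuis only and does not bear on self-report.
- **Pre-operative weight loss.** A reader might infer that it all happens after disclosure and so may differ by arm. The article says that "patients in both arms of the study are projected to the same pre-surgical weight loss", which is an expectation, but nowhere says that the loss starts only after allocation. The preoperative programme already includes a dietician.
- **HbA1c and weight.** Both are scheduled at screening. Their order relative to allocation within t = -2 is not stated, so neither a defect nor a safe pre-allocation value can be claimed.

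**Conclusion.** The point holds for the self-reported secondary outcomes. By the article's own schedule, the psychological questionnaires, GIQLI, and the dietary and satiety list have no pre-randomisation baseline, and the first scores are given after the patient knows the operation.

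Whether this causes bias, and how much, cannot be derived from the document. Under the assumed shifts of 0.1 to 0.3 SD, the false-positive rate would run from about 9% to 78% for change scores and from about 6% to 55% for a baseline-adjusted comparison. A follow-up-only comparison stays at 5% if the shift is confined to baseline. These figures show sensitivity and are not an estimate for this trial. The primary outcome, HbA1c at 12 months, is not shown to be affected. The change is worth making because it is cheap and the risk is avoidable.

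**What to change.** **Patients still to be enrolled.** Have the existing questionnaires completed after consent and before the randomisation is performed, and amend Table 1 to show this order. Either the forms are filled in at the clinic before the surgeon randomises, or the randomisation waits until they are done. No new measurement is needed. Under Trial status the article reports 86 + 14 = 100 patients enrolled at the two current centres out of 220, so at most 220 − 100 = 120 could benefit, counted at the time of writing.

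**Patients already enrolled.** Report that their baseline followed disclosure. Add a sensitivity comparison of follow-up scores between arms that neither subtracts nor adjusts for that baseline. An adjusted analysis may stay alongside it, since it corrects for chance imbalance in an unstratified trial.

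**Cost.** There are three costs:

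- A small change in clinic logistics. The operation is known somewhat later if randomisation waits, or the baseline lies further from surgery if the forms move to screening.
- Two baseline timings within one trial, to be recorded per patient and flagged in the analysis.
- Some loss of precision in the unadjusted sensitivity analysis, with standard errors about 5% to 40% larger than under adjustment over the assumed range of r.
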